# Plan of Investigation

## Study Schema

STEMI

BHI

Catheter Lab for PPCI

Bivalirudin

Prasugrel 60mg bolus

Prasugrel 10mg daily

24hours

& 30day

Clinical

Follow-up

Multiplate Platelet Function Assessment

**TIME 0**

Admission

**TIME 1**

Immediate

Post PCI

**TIME 2**

1hours

Post PCI

**TIME 3**

2hours

Post PCI

**TIME 4**

24hours

Post PCI

## Study Design

This is a prospective observational study.

## Outcomes

### Primary Outcomes

The primary outcome for study is the platelet function assessment measured in peripheral ‘whole’ blood. Functional assessment of ADP receptor, arachidonic acid pathway, and thrombin related platelet activation will be measured using a multiple electrode analyser (MEA – Multiplate platelet function analysis).

Platelet function (measured in peripheral ‘whole’ blood, see above) will be assessed on arrival at hospital, at completion of the PPCI, 1, 2 and 24 hours after the completion of the PPCI. These measurements will allow the study to test how the profile of platelet function changes over the period of time in which the effect of bivalirudin wanes and prasugrel increases, by assessing the interaction between door-to-balloon time and time-after-completion of PPCI.

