# Definitions

STEMI Determined by a 12-lead ECG at the time of presentation with/without chestpain demonstrating either 1mm ST elevation in two contiguous leads or new-onset left bundle branch block.

Low platelet response Determined by comparison of ADPtest result from multiplate analyzer against a reference population of patients receiving aspirin and a P2Y12 receptor inhibitor, defined by Sibbing et al (ref). The lowest quintile (20%) of the population were identified to have significantly increased risk of adverse thrombotic events (i.e. stent thrombosis).

MACE A composite of target vessel and target lesion revascularization, cardiac death, and non-fatal myocardial infarction.

Stent thrombosis Using the Academic Research Consortium (ARC) definition(1) events are defined as definite, probable or possible and early (0-30days), late (31-360days) or very late (>360days). Definite stent thrombosis must be confirmed by angiographic or autopsy evidence of thrombosis/vessel occlusion. Probable stent thrombosis is defined as unexplained death within 30days of the index procedure, or evidence of acute myocardial infarction involving the target vessel territory. Possible stent thrombosis is classified as all unexplained death occurring at least 30days from the procedure.

Bleeding Using the GUSTO bleeding score(2) where events are classified as severe (deadly bleeding; intracerebral bleeding or substantial hemodynamic compromise requiring treatment), moderate (requiring transfusion) or mild (bleeding not requiring transfusion or causing hemodynamic compromise).

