## Sample size and justification

The primary analysis will be a mixed model regression (see below). Calculation of the sample size needed to detect a statistically significant effect of a key predictors in such analyses require the following assumptions to be defined (parameter = estimate):

r-squared for full model = 0.25

r-squared for reduced model (excluding key predictor) = 0.20

number of predictors in full model = 8

number of predictors being tested = 1

Because two key predictors will be tested (see below), a significance level of 0.025 will be adopted (Bonferroni correction) giving a nominal hypothesis test at p<0.05 for each predictor. For 80% power, the above assumptions require a target sample size of 135. This target sample size needs to be further adjusted by the relative efficiency of the analysis, i.e. to take into account the three repeated measures. Estimating the relative efficiency requires further assumptions about the correlations between the repeated measures; for correlations ranging from 0.5 to 0.8, the relative efficiency varies from 1.25 to 1.50. Taking the lower estimate of relative efficiency gives a final target sample size of 108 (i.e. 135/1.25).

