## Analysis plan

The primary analysis will be a mixed model regression to take into account the three repeated measures of platelet function at 1, 2 and 24 hours after completion of PPCI. Platelet function on arrival at the hospital, and platelet function after completion of PPCI, are not expected to be influenced by door-to-balloon time and will be entered as covariates. Other potential confounding factors influencing platelet function (e.g. peak troponin, age, gender, diabetic status) will also be entered as covariates. Two key predictors will be tested in the model, namely the effects of (a) door-to-balloon time and (b) platelet function on arrival at the hospital.

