## Research Procedures

### In-patient Procedures

Platelet function will be assessed at baseline and multiple time points after completion of the PPCI procedure, i.e. 0, 1, 2 and 24 hours. Platelet function will be assessed using a multiple electrode analyser (MEA – Multiplate platelet function analysis). This technique has been well validated for assessment of the anti-platelet effect of ADP receptor inhibitors and aspirin, offering very useful information regarding the future risk of significant adverse events(9).

MEA-derived platelet function is assessed using ‘whole blood’ samples; however, platelets are very sensitive to mechanical disruption and have a tendency to aggregate with time after obtaining the blood sample, impairing assessment. Consequently, platelet function testing requires careful sampling and timely analysis. MEA is a ‘point of care’ system and therefore we propose that the multiplate platelet function analyser will be installed in the catheter laboratory, enabling us to undertake immediate analysis of blood samples. [name], Senior lecturer and Consultant in Haematology, has significant expertise in the field and will kindly support us in the set-up of the device.

We propose that patients will provide ‘assent’ at the time of formal consent for the PPCI procedure. The MEA testing requires: a single 3ml blood sample to be withdrawn from the arterial sheath (1x 3ml Hirudin sample), at the time of routine blood sampling, before starting the PPCI; the second sample (Time 1) will be taken at the end of the procedure; the subsequent samples (Time 2-4) will be obtained 1, 2 & 24 hours following completion of the PPCI using standard venepuncture technique. Where ever possible venepuncture will be scheduled to co-incide with clinically required phlebotomy. Immediate assessment of platelet activity (arachidonic acid, thrombin receptor, thromboxane receptor & ADP-receptor activation assessment – ASPI, TRAP, U46119 & ADP tests) will be undertaken using the ‘in-lab’ multiplate analyser. Formal written consent for measurement of platelet activity will be requested within 24 hrs of recruitment.

Clinical data (see 7.3.2 and 7.3.3) will be gathered at 24hours and at time of discharge.

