## Source Data

The following will be considered as source data:

- Participant medical notes will be the source for participant contact details, medical history and routinely collected clinical data and the clinical assessments;
- NHS laboratory databases will be the source data for blood results

The ‘in-lab’ multiplate platelet function analyser provides an averaged platelet function assessment generated from duplicate measurements. We intend to use the raw data (i.e. duplicate sample results) for analysis.

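### The primary outcome covers three assay pathways with no primary variable named, while the 0.025 significance level corrects only for the two predictors

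*Protocol*

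**What the plan says.** - **Outcome.** Section 7.3.1 (Primary Outcomes) gives the primary outcome as a platelet function assessment in whole blood: "Functional assessment of ADP receptor, arachidonic acid pathway, and thrombin related platelet activation will be measured". None of the three pathways is singled out.
- **Tests run.** Section 8.3.1 (In-patient Procedures) lists the laboratory tests as "ASPI, TRAP, U46119 & ADP tests".
- **Alpha.** Section 7.5 (Sample size and justification): "Because two key predictors will be tested (see below), a significance level of 0.025 will be adopted (Bonferroni correction". No other source of multiplicity is counted.
- **Tests planned.** Section 7.6 (Analysis plan): "Two key predictors will be tested in the model, namely the effects of (a) door-to-balloon time and (b) platelet function on arrival". The assay behind predictor (b) is not named either.
- **Pointers to ADP.** Section 3 (Definitions) defines low platelet response by one assay: "Determined by comparison of ADPtest result from multiplate analyzer against a reference population". The hypothesis in section 6 concerns incomplete P2Y12 blockade.
- **Duplicates.** Section 8.6 (Source Data) notes that the analyser supplies an average of two readings, then says: "We intend to use the raw data (i.e. duplicate sample results) for analysis". Section 7.6 describes a "mixed model regression to take into account the three repeated measures of platelet function", and section 7.5 adjusts the sample size for three repeated measures.

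**The concern.** A Bonferroni factor of two fits a single outcome variable tested for two predictors. Section 7.3.1 supplies three candidate variables. Nothing in the protocol prevents the model from being fitted to each assay and the primary conclusion from being drawn from whichever is significant. The 0.025 level would not hold the overall error at 5% under that use.

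The second, lesser matter is the unit of analysis. Two readings at each of 1, 2 and 24 hours make six records per patient and assay, whereas sections 7.5 and 7.6 account for three. Two readings of one blood sample share whatever is particular to that sample, so they are not independent given the patient unless the model says otherwise. This could affect comparisons over time within patients, such as the door-to-balloon by time interaction announced in 7.3.1.

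**Working it through.** **1. The protocol's own figure.** Two predictors, overall level taken as 0.05: 0.05/2 = 0.025. This reproduces. For one outcome variable and two independent tests, 1 − (1 − 0.025)² = 0.0494; the bound is 2 × 0.025 = 0.05. The correction does its job for one assay.

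**2. Three assays, two predictors.** 3 × 2 = 6 tests, each at 0.025 two-sided (the protocol does not state sidedness), any positive counting.

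- Independent tests: 1 − (1 − 0.025)⁶ = 0.141.
- Bound under any dependence: 6 × 0.025 = 0.15.
- Correlated assays: 300,000 simulated sets of z-tests, equal correlation r between assays, independence between the two predictors. The protocol gives no value for r, so a range is shown.

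| Assumed r | Family-wise error |
| --- | --- |
| 0 | 14.1% |
| 0.5 | 12.6% |
| 0.7 | 11.0% |
| 0.9 | 8.5% |
| 0.99 | 6.1% |

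Correlation shrinks the excess, but even at 0.99 the rate is above 5%.

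**3. What correcting over assays would cost instead.** The level would be 0.05/6 = 0.00833. With the inputs of section 7.5, f² = (0.25 − 0.20)/(1 − 0.25) = 0.0667, and an F test on 1 and N − 9 degrees of freedom with noncentrality f² × N:

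- at 0.025: N = 146 for 80% power; power at 135 is 76.7%;
- at 0.00833: N = 186 for 80% power; power at 135 is about 63%.

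Dividing by the protocol's relative efficiency of 1.25 gives 117 and 149. This formula does not return the protocol's 135. That is a separate matter; the comparison here is between two results of the same formula.

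**4. Duplicates, if entered with a patient intercept only.** Let s be the share of within-patient variance (single reading) that lies between blood samples, and 1 − s the duplicate error. For an interaction with time, per reading:

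- correct variance: 2 × [s + (1 − s)/2] = 1 + s;
- variance the model would use, pooling about 2n between-sample and 3n duplicate degrees of freedom: [2(1 + s) + 3(1 − s)]/5 = 1 − s/5;
- ratio of standard errors: √[(1 − s/5)/(1 + s)].

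The type I error comes from simulation with 108 patients, 3 times and 2 readings, no true interaction, a nominal 2.5% level, and 50% or 80% of variance between patients.

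| Assumed s | SE ratio | Type I error, raw duplicates |
| --- | --- | --- |
| 0 | 1.00 | about 2.5% |
| 0.2 | √(0.96/1.2) = 0.89 | about 5% |
| 0.5 | √(0.90/1.5) = 0.77 | 10% to 11% |
| 0.8 | √(0.84/1.8) = 0.68 | about 19% |

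Using the mean of the duplicates gave 2.1% to 2.9%.

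**5. The two key predictors.** Each has one value per patient, so in balanced data its test compares patient averages, which are the same whether or not duplicates are averaged first. A simulation at nominal 5% gave 4.4% to 5.2%: no inflation.

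**The case against.** Several points against this are fair.

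- **No rule that any assay counts is stated.** The study is observational, its primary objective is partly descriptive, and sections 3 and 6 already point to the ADP assay. Section 9 promises an analysis plan before any inferential analysis, and that plan may name the assay. This stands as a condition on the figures. It does not remove the point: the protocol itself fixes both the outcome and the significance level, and the two do not match. The analysis plan is to be written during data collection, when analyser results are already being read in the laboratory, so naming the assay in the protocol avoids any question of a choice informed by results.
- **Four assays and eight tests.** A reader might infer from the list in 8.3.1 that the primary outcome comprises four assays. The documents do not support that. Section 8.3.1 lists tests to be run; 7.3.1 defines the primary outcome and lists three pathways.
- **Standard errors that are certainly too small.** A reader might infer this from 8.6. The documents do not support it. Section 7.6 gives no random-effects structure, a detail commonly left to the analysis plan, and raw duplicates with a sample-level term give valid standard errors. The interaction that would suffer is not one of the two key predictors in 7.6, and 7.5 assigns it no alpha.

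**Conclusion.** The concern holds in a limited form. The primary outcome has three candidate variables and the significance level allows for one. If each assay is tested for both predictors at 0.025 and any positive result is taken as the finding, the family-wise error lies between about 8.5% and 14% for correlations from 0.9 down to 0, with a bound of 15%, against an intended 5%. This rests on two-sided tests, on assumed correlations, on reading 0.05 as the overall level, and on confirmatory use of every assay, which the text permits but does not state.

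The duplicates are a conditional, secondary point. Only if they are treated as independent given the patient does the interaction test become anti-conservative: about 5% to 19% at nominal 2.5% when 20% to 80% of within-patient variance lies between samples, with no inflation when none does. That variance range is assumed. The tests of door-to-balloon time and of platelet function on arrival are essentially unaffected in balanced data.

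**What to change.** - **Section 7.3.1:** state that the primary variable is the ADPtest result at each time point, and that the other assays are secondary and carry no alpha. The ADPtest is the assay that defines low response in section 3 and measures the P2Y12 effect in the hypothesis.
- **Section 7.6:** say that platelet function on arrival, as key predictor (b), is measured by the same assay.
- **Section 8.6:** say that the analysis uses the mean of the duplicates, with the raw readings kept for quality control and for estimating assay error. Alternatively, if the readings are modelled singly, add a random effect for blood sample within patient.
- **Sections 7.3.1 and 7.6:** reconcile whether the door-to-balloon by time interaction is tested.

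The cost is a few sentences, with no new data and no extra patients on this account; 0.025 for two tests on one assay keeps the overall error at or below 5%. The downside is that the arachidonic acid and thrombin-related assays can no longer support the primary conclusion.

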### Secondary Outcomes

Incidence of adverse clinical events at 24hours and 30days, including:

- Major adverse cardiac events (MACE) – a composite of target vessel revascularisation, target lesion revascularisation, non-fatal myocardial infarction, and cardiac death
- Bleeding complications – using TIMI major and minor bleeding criteria
- Stent thrombosis (ARC definition, see Section 3)

### Confounding variables

We will measure and record confounding variables associated with the characteristics of the index MI and platelet reactivity. Variables will include: timing of symptoms/presentation relative to initiation of treatment, the maximum CKMB/Troponin T, age, gender, co-existent diabetes, concomitant treatments, high sensitivity CRP and WCC.

## Study Population

We propose prospective recruitment of 108 STEMI patients undergoing PPCI at the BHI, receiving standard care with prasugrel loading on admission and subsequent bivalirudin bolus and infusion therapy peri-procedurally. Assuming a 60% recruitment rate, we would anticipate completing recruitment within 6 months.

### Inclusion Criteria

A participant may enter the study if ALL of the following apply:

- Admitted with acute STEMI
- Treated with PPCI at the time of index procedure

### Exclusion Criteria

A participant may not enter the study if ANY of the following apply:

1. Unable to take prasugrel
2. Unable to take bivalirudin
3. Haemodynamic instability/cardiogenic shock
4. Current treatment with Clopidogrel or Prasugrel

## Sample size and justification

The primary analysis will be a mixed model regression (see below). Calculation of the sample size needed to detect a statistically significant effect of a key predictors in such analyses require the following assumptions to be defined (parameter = estimate):

r-squared for full model = 0.25

r-squared for reduced model (excluding key predictor) = 0.20

number of predictors in full model = 8

number of predictors being tested = 1

Because two key predictors will be tested (see below), a significance level of 0.025 will be adopted (Bonferroni correction) giving a nominal hypothesis test at p<0.05 for each predictor. For 80% power, the above assumptions require a target sample size of 135. This target sample size needs to be further adjusted by the relative efficiency of the analysis, i.e. to take into account the three repeated measures. Estimating the relative efficiency requires further assumptions about the correlations between the repeated measures; for correlations ranging from 0.5 to 0.8, the relative efficiency varies from 1.25 to 1.50. Taking the lower estimate of relative efficiency gives a final target sample size of 108 (i.e. 135/1.25).

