# Hypothesis and Study Objectives

Minimising the time from STEMI symptom onset to definitive treatment, with mechanical revascularisation, remains a major focus of attention in optimising the PPCI service. We hypothesise that continued reductions in the “door to balloon” time (time from hospital admission to achieving an open artery in the catheter laboratory) may result in some patients undergoing PPCI with incomplete P2Y12 blockade, leading to an increase in risk of early thrombotic events. We speculate that the rapid restoration of coronary flow achieved with PPCI may offer inadequate time to achieve platelet inhibition with prasugrel, prior to the loss of the anti-thrombin effect of bivalirudin.

The primary objective of the study is to describe variation in platelet activity at the end of the PPCI and to quantify the relationship between “door to balloon time” and platelet function in the first 24 hours after completing the PPCI.

The secondary objective of the study is to test the hypothesis that patients with high platelet activity at the time of arrival at hospital (baseline) achieve less platelet inhibition in the first 24 hours following commencement of anti-thrombotic and anti-platelet therapy.

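### Section 7.5 adopts a Bonferroni level of 0.025 but misdescribes it as a p<0.05 test of each predictor; it should say 0.025 per predictor and at most 0.05 for the pair

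*Protocol*

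**What the plan says.** Protocol section 7.5 (Sample size and justification) says that "a significance level of 0.025 will be adopted (Bonferroni correction) giving a nominal hypothesis test at p<0.05 for each predictor". The reason given in the same sentence is that two key predictors are to be tested. The section then gives 135 as the number needed for 80% power and divides it by 1.25, for the repeated measures, to reach 108.

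Section 7.6 (Analysis plan) identifies the tests: "Two key predictors will be tested in the model, namely the effects of (a) door-to-balloon time and (b) platelet function on arrival at the hospital". It gives no significance level. Section 6 (Hypothesis and Study Objectives) places the second of these under the secondary objective: "The secondary objective of the study is to test the hypothesis that patients with high platelet activity at the time of arrival at hospital" achieve less platelet inhibition in the first 24 hours. It gives no significance level either. Section 9 (Analyses) leaves further detail to a statistical analysis plan.

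**The concern.** A Bonferroni correction divides the overall error between the tests. With two tests and an overall 0.05, each is judged at 0.025, and 0.05 is the bound for the pair. The clause "giving a nominal hypothesis test at p<0.05 for each predictor" attaches 0.05 to the single test instead. A nominal level normally means the one applied to the raw p-value, so the clause taken literally describes an uncorrected test.

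This is the only decision threshold in the protocol for the two tests of the primary model. It is a misstatement in the text, not a detail left for later, so it could be carried into the analysis plan unchanged. An analyst who followed the trailing clause would lose the multiplicity control that the first half of the sentence sets up.

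**Working it through.** **Inputs, all from section 7.5.** "r-squared for full model = 0.25"; "r-squared for reduced model (excluding key predictor) = 0.20"; 8 predictors in the full model, 1 tested; 80% power; N = 135 before and 108 after the repeated-measures adjustment.

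**1. The plan's own figures.** 135/1.25 = 108 reproduces exactly. For 135, the standard calculation is the partial F-test for an increment in R-squared:

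- Effect size: f² = (0.25 − 0.20)/(1 − 0.25) = 0.0667.
- Degrees of freedom: 1 and N − 9.
- Noncentrality: N × f², which is 135 × 0.0667 = 9.0 at N = 135.

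| Level per predictor | N for 80% power | N/1.25 | Power at N = 135 |
|---|---|---|---|
| 0.025 | 146 | 116.8, so 117 | 76.7% |
| 0.05 | 120 | 96 | 84.5% |

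The stated 135 is not reproduced at either level. It gives 80% power only at a level of about 0.033.

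**2. Other formulas.** Several non-standard variants were tried. Dividing by 1 − 0.20 instead of 1 − 0.25 (f² = 0.05/0.80 = 0.0625), with smaller noncentrality definitions, gives 135 or 137 at 0.05 with one predictor tested, and 132 or 135 at 0.10 with two tested. No variant tried at 0.025 gave 135. The protocol does not name its formula, so the number cannot show which level was used.

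**3. Family-wise error for two tests.** If they are independent, the error is 1 − (1 − α)²:

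- α = 0.025: 1 − 0.975² = 0.0494 (bound 2 × 0.025 = 0.05).
- α = 0.05: 1 − 0.95² = 0.0975 (bound 2 × 0.05 = 0.10).
- Ratio: 0.0975/0.0494 = 1.97.

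The protocol does not give the correlation between the two test statistics, so a range is assumed (bivariate normal, two-sided):

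| Correlation | 0.025 each | 0.05 each |
|---|---|---|
| 0 | 4.94% | 9.75% |
| 0.3 | 4.84% | 9.51% |
| 0.5 | 4.65% | 9.07% |
| 0.8 | 4.02% | 7.81% |

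**4. How often the wording could matter.** Under the stated effect at N = 135, the chance that a given predictor's p-value lies between 0.025 and 0.05 is 84.5% − 76.7% = 7.8%. With no effect it is 5% − 2.5% = 2.5%.

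**The case against.** The strongest reply is that the sentence does not set two rival rules. Its operative part adopts 0.025, names the method and gives the reason. The 0.05 phrase only describes the outcome, and it could be rescued by reading it as a cut-off for a doubled (adjusted) p-value. An analyst who reads the whole sentence would test each predictor at 0.025, and the family-wise error would be held as intended. This stands, and it limits the point to a misstatement that needs correcting. It does not remove the point, because the protocol never mentions adjusted p-values and the phrase is wrong as written.

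Stronger readings are tempting, but the document does not support them:

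- **A p-value between 0.025 and 0.05 is both significant and not significant.** This follows only if the trailing phrase overrides the adopted level. On the natural reading such a result is simply not significant.
- **The 0.025 might be a one-sided equivalent of a two-sided 0.05.** Section 7.5 ties 0.025 to the testing of two predictors, and an R-squared increment is tested by an F-test, which has no direction.
- **The 135 shows that 0.05 was used.** Some non-standard formulas at 0.05 do give it, but the protocol states no formula and the standard one gives 120.
- **Bonferroni should be replaced by Holm's procedure.** Bonferroni is valid and was the stated choice. It also gives matching confidence intervals directly, which suits a study whose primary objective includes quantifying a relationship.

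It is also fair to note that the study is observational, that its primary objective is partly descriptive, and that a fuller analysis plan is promised. These make it less likely that the phrase alone decides a conclusion.

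**Conclusion.** The point holds as an error of wording in the protocol's only decision threshold. The intended rule is most likely 0.025 per predictor and at most 0.05 for the pair, and the trailing clause misstates it. If the clause were followed literally, the family-wise error would be 9.75% for independent tests, and 7.8% to 9.5% for correlations of 0.8 down to 0.3, instead of at most 5%. These figures rest on two two-sided tests and an assumed correlation. They measure the cost of the literal reading, not of the rule that section 7.5 adopts.

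Neither the rest of the protocol nor the stated sample size settles the wording. The failure of 135 to follow from 0.025 is a separate matter. It is used here only to show that the number cannot act as a tie-breaker.

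**What to change.** In section 7.5, delete "giving a nominal hypothesis test at p<0.05 for each predictor" and write instead: *each key predictor is declared significant only if its unadjusted two-sided p-value is below 0.025 (with 97.5% confidence intervals), so that the family-wise error is at most 0.05.* Carry the same rule into the analysis plan before any inferential analysis, so that the threshold cannot appear to have been chosen after seeing the data. Holm's procedure, in which the smaller p-value is compared with 0.025 and, if significant, the other with 0.05, is an optional alternative. It also keeps the family-wise error at or below 0.05.

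The new sentence should not imply that 135 follows from 0.025. Once 0.025 is confirmed, restate the power for 135 as about 77% with the stated inputs, before the relative-efficiency adjustment, or state the formula that produced 135.

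The cost is one sentence on the threshold and one on power. No extra patients or data are required. The threshold is stricter than the literal p<0.05 reading and the same as the level already adopted.

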## Planned recruitment rate

The study requires serial measurement of platelet activity upto 24 hours post PPCI and therefore recruitment will be limited to weekdays between 0800-1600hrs. We anticipate completing recruitment within a 12 month period, with a minimum weekly recruitment rate of 2 patients.

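### The sample size does not follow from its stated inputs: the base figure should be 146, not 135, and 108 patients give about 73% to 85% power over the protocol's own correlation range

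*Protocol*

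**What the plan says.** Protocol section 7.5 (Sample size and justification) sizes the study for the test of a single key predictor in a regression. The inputs are "r-squared for full model = 0.25", "r-squared for reduced model (excluding key predictor) = 0.20" and "number of predictors in full model = 8", with one predictor tested. Because there are two key predictors, the level is set at 0.025 by Bonferroni, which the section describes as "giving a nominal hypothesis test at p<0.05 for each predictor". It then states "For 80% power, the above assumptions require a target sample size of 135".

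Next it allows for the three repeated measures, which section 7.6 (Analysis plan) places at 1, 2 and 24 hours after the procedure: "for correlations ranging from 0.5 to 0.8, the relative efficiency varies from 1.25 to 1.50". It takes the lower efficiency and reaches 135/1.25 = 108, which section 7.4 (Study Population) adopts as the recruitment target. The efficiency formula is not given.

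**The concern.** Every input to the first step is printed, so the result can be checked, and it does not come out at 135. The second step pairs two correlations with two efficiencies, and only one of the pairs fits the usual formula for three measures. The protocol chose the lower efficiency in order to be cautious, so an error at that end removes the protection it was meant to give.

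At stake is the claim of 80% power for each of the two key predictors, door-to-balloon time and platelet function on arrival. If a predictor test is not significant, readers will weigh that result against the stated power.

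**Working it through.** **Inputs (all from section 7.5, except the three times from 7.6).** R-squared 0.25 full and 0.20 reduced; 8 predictors; 1 tested; level 0.025; power 80%; three measures; correlation ρ from 0.5 to 0.8.

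**Step 1: base sample size.**
- Effect size: f² = (0.25 − 0.20)/(1 − 0.25) = 0.0667.
- Test: F with 1 and n − 9 degrees of freedom, noncentrality n·f².
- Smallest n with at least 80% power at 0.025: **146** (80.2%).
- Power at n = 135: **76.7%**.
- Hand check by the normal approximation: (2.241 + 0.842)²/0.0667 = 142.6, so 143. At n = 135, √(135 × 0.0667) = 3.0 and Φ(3.0 − 2.241) = 77.6%.

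Attempts to reproduce 135:
- At level 0.025, other noncentrality conventions give 153 to 155 and approximations to the noncentral F give 143. A Fisher-z partial-correlation calculation gives about 156, and a Šidák level gives 145.
- At level 0.05 the exact answer is 120. Other conventions and approximations give 117 to 131.
- With f² divided by 0.80 or 0.95 instead of 0.75, the results are 155 and 184 at level 0.025, and 128 and 152 at level 0.05.
- For 135 to give 80% power the level would have to be about 0.033, which the protocol does not mention.

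**Step 2: relative efficiency.** For a patient-level predictor and the mean of three equally correlated measures, RE = 3/(1 + 2ρ):
- ρ = 0.5: 3/2.0 = 1.50
- ρ = 0.7: 3/2.4 = 1.25
- ρ = 0.8: 3/2.6 = 1.154

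The protocol's 1.50 at 0.5 matches exactly. Its 1.25 belongs to 0.7, not 0.8. A first-order autoregressive structure gives 1.67 at 0.5 and 1.22 at 0.8, so it does not yield the stated range either.

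**Step 3: what 108 delivers.** The plan's last division is correct: 135/1.25 = 108. The power of 108 patients uses noncentrality f² × 108 × RE at level 0.025. The two power figures use degrees of freedom based on 108 patients and on the effective n.

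| ρ | RE | Effective n (108 × RE) | Power | n needed (146/RE) |
|---|---|---|---|---|
| 0.8 | 1.154 | 124.6 | 72.7% to 72.9% | 127 |
| 0.7 | 1.25 | 135 | 76.4% to 76.7% | 117 |
| 0.5 | 1.50 | 162 | 84.2% to 84.6% | 98 |

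Power of 80% needs an effective n of about 146, so RE of about 146/108 = 1.35, which corresponds to ρ of about 0.61 or lower.

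**The case against.** **The inputs are soft.** The R-squared values are round planning figures with no source given. Holding the full-model value at 0.25, an increment of about 0.054 instead of 0.050 would give 80% at n = 135, and about 0.058 would give 80% for 108 patients at ρ = 0.8. The study is observational, and part of its primary objective is descriptive and needs no power. This is fair, and it limits the practical weight of the point. It does not make 135 the answer to the inputs as printed.

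**A slip in the correlation.** If 0.8 was meant to be 0.7, the efficiency of 1.25 is right. The first step remains wrong, and power at 108 is 76% to 77%.

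**Stronger readings that the protocol does not support:**
- A reader might infer that the study simply has 73% power. That is the figure at one end of the correlation range and under equal correlations; at ρ = 0.5 the power is above 80%.
- A reader might infer from "giving a nominal hypothesis test at p<0.05 for each predictor" that each predictor will be tested at 0.05 and the family-wise error inflated. The same sentence fixes the level at 0.025 explicitly, so this is a wording slip.
- A reader might infer that recruitment cannot reach 108, since 2 × 52 = 104. Section 8.8 says "We anticipate completing recruitment within a 12 month period, with a minimum weekly recruitment rate of 2 patients", and a minimum that falls four short does not contradict the target. Section 7.4 does conflict with it on duration: "Assuming a 60% recruitment rate, we would anticipate completing recruitment within 6 months". That is a feasibility matter with no bearing on power.

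**Conclusion.** The point holds. The base sample size is wrong on the protocol's own inputs: 146 is required, and 135 gives 76.7% power. This step needs no assumption about correlation. The efficiency range is also mismatched, because 1.25 does not cover the stated upper correlation of 0.8. Together they mean that 108 patients give about 73% to 85% power over the range 0.8 to 0.5, with 80% reached only at a correlation of about 0.6 or lower.

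The second part assumes equal correlations among the three measures. The protocol does not state this, but it is the structure that matches its own 1.50 at 0.5. All the power figures assume complete samples, since the calculation has no allowance for missing ones. They apply to an effect averaged over the three times. They are not the power for the interaction between door-to-balloon time and time after the procedure, which section 7.3.1 (Primary Outcomes) also says will be assessed.

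The error affects the justification of the sample size and does not invalidate the planned analysis.

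**What to change.** In section 7.5:
- Restate the base sample size as 146.
- Restate the relative efficiency as 1.15 to 1.50 for correlations of 0.8 down to 0.5, and name the equal-correlation assumption.
- State that 108 patients give about 73% to 85% power at 0.025 per predictor, for the effect averaged over the three times and not for its interaction with time.
- Replace the clause on the nominal level with wording that each predictor is tested at 0.025, which holds the family-wise error at 0.05.

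The Bonferroni scheme for the two key predictors can stay as it is. The cost is protocol wording and a less favourable power statement. If the sponsor wishes to keep 80% at correlation 0.8, the target becomes 146/1.154 = 127, which is 19 more patients.

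Separately, reconcile the 6-month recruitment period in section 7.4 with the 12 months in sections 8.4 (Duration of Study) and 8.8 (Planned recruitment rate).
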